# Counting on U training to enhance trusting relationships and mental health literacy among business advisors: protocol for a randomised controlled trial

**DOI:** 10.1186/s12888-022-04034-7

**Published:** 2022-06-15

**Keywords:** Mental health first aid, Depression, Prevention, Mental health conditions, Relationships, Business advisors, SMEs

## Abstract

**Background:**

Financial distress is thought to be a key reason why small-medium enterprise (SME) owners experience higher levels of mental health conditions compared with the broader population. Business advisors who form trusting, high-quality relationships with their SME clients, are therefore well placed to: (1) help prevent/reduce key sources of financial distress, (2) better understand the business and personal needs of their clients and, (3) recognise the signs and symptoms of mental health conditions and encourage help-seeking where appropriate. The aim of this study is to compare the effectiveness of relationship building training (RBT) combined with mental health first aid (MHFA) training for business advisors with MHFA alone, on the financial and mental health of their SME-owner clients.

**Methods:**

This is a single blind, two-arm randomised controlled trial. Participants will be business advisors who provide information, guidance and/or assistance to SME owner clients and are in contact with them at least 3 times a year. The business advisors will invite their SME-owner clients to complete 3 online surveys at baseline, 6- and 12-months. Business advisors will be randomised to one of two conditions, using a 1:1 allocation ratio: (1) MHFA with RBT; or (2) MHFA alone, and complete 3 online surveys at baseline, 2- and 6-months. Primary outcomes will be measured in the business advisors and consist of the quality of the relationship, stigmatizing attitude, confidence to offer mental health first aid, quality of life and provision of mental health first aid. Secondary outcomes will be measured in the SME owners and includes trust in their business advisors, the quality of this relationship, financial wellbeing, financial distress, psychological distress, help-seeking behaviour, and quality of life. To complement the quantitative data, we will include a qualitative process evaluation to examine what contextual factors impacted the reach, effectiveness, adoption, implementation, and maintenance of the training.

**Discussion:**

As there is evidence for the connections between client trust, quality of relationship and financial and mental wellbeing, we hypothesise that the combined RBT and MHFA training will lead to greater improvements in these outcomes in SME owners compared with MHFA alone.

**Trial registration:**

ClinicalTrials.gov: NCT04982094. Retrospectively registered 29/07/2021. The study started in February 2021 and the recruitment is ongoing.

**Supplementary Information:**

The online version contains supplementary material available at 10.1186/s12888-022-04034-7.

## Background

Small to Medium Enterprises (SMEs) account for 99% of all businesses in Australia and at least 95% of enterprises in all OECD countries [1, 2]. They contribute significantly to Australia’s social and economic prosperity, with small businesses employing approximately 4.7 million people and accounting for 41% of total employment [3]. Despite their importance, SME owners face significant ongoing challenges. Externally, these challenges include increasing market volatility, lending restrictions, extensive legislative reform, and rapid technological advancements, while internally they include monitoring cash flow, managing staff, and ensuring the smooth administration of the business [2, 4]. These challenges can generate significant financial pressure and in turn, financial distress (or a lack of financial wellbeing) among SME owners [5].

Financial distress, the SME owner's working conditions (e.g., long hours, burden of responsibility, isolation, obligation to work when sick) and their low rates of help seeking are thought to be why this group experiences higher levels of mental health conditions compared with the broader population [5–11]. The COVID-19 pandemic has also triggered a sharp increase in psychological distress among small business owners, as a recent study commissioned by the Australian Government shows 1 in 3 rated their mental health as fair to poor during the first three months of the pandemic [12]. Developing strategies that can help alleviate the financial distress experienced by SME owners, but at the same time encourage owners to seek help for potential mental health conditions, are therefore critical for protecting and promoting their mental health.

One group that has the potential to address financial distress and act as an intermediary between SME owners and mental health services are business advisors, particularly accountants and bookkeepers. SME owners draw on the technical expertise provided by business advisors on a regular basis, and advisors can often form trusting, long-term relationships with their clients [13]. Intuitively, the formation of these more trusting, longer-term relationships provides the potential for business advisors to better understand the business and personal challenges faced by SME owners, to identify the early signs of mental health conditions and to take action to help alleviate the sources of financial distress.

Mental health literacy programs, such as Mental Health First Aid (MHFA) training, are a key strategy for the early identification of mental health conditions (e.g., depression, anxiety) and are designed to reduce their impact (i.e., secondary, and tertiary prevention) rather than preventing them from occurring in the first instance (i.e., primary prevention) [14–17]. A systematic review has shown that MHFA training can improve knowledge of mental health and the treatments available, recognition of mental health conditions and reduce stigma [18]. This training is popular in the health and human service sectors, and one observational study on financial counsellors has been conducted, however it is not known to what extent their clients received mental health first aid-related advice and support [9, 18–23].

The aim of the current study called Counting on U is to evaluate the effectiveness of relationship building training (RBT) combined with mental health first aid (MHFA) for business advisors, compared with MHFA alone, on the relationship between business advisors and their SME-owner clients, and the financial and mental health wellbeing of their clients [20]. The RBT has been guided by primary prevention principles and aims to equip business advisors with the skills to: (1) form more trusting relationships with their clients so that SME owners feel more comfortable disclosing financial difficulties and/or mental health conditions, (2) better understand the needs of the business and the business owner and thus, (3) prevent/reduce the financial distress experienced by SME owners.

In view of the above, we have formulated a set of hypotheses for testing in the current study. We expect that for business advisors randomised to the RBT and MHFA training compared with MHFA alone: (1) will be in a better position to recognise signs of distress in their SME-owner clients, so the quality of their relationship will be stronger, (2) better understand how financial distress may lead to poor mental health, and decrease any stigmatizing attitudes they may have (e.g., depression is a sign of personal weakness) and, (3) be more confident to provide mental health first aid and the frequency in which they do so, will be greater. SME owners whose advisors undertake the RBT and MHFA, compared with MHFA alone will report: (1) greater trust in their business advisor, (2) the quality of the relationship with their business advisor will be stronger, (3) improved financial wellbeing, psychological distress, and quality of life, and (4) greater help seeking intentions and behaviour. This will be an Australian and New Zealand wide study targeting eligible participants across all regions, urban/regional/rural and states, to ensure SME owner clients such as farmers in drought-stricken areas, to city coffee shop owners, have an opportunity to benefit from the program.

## Methods/design

### Study design

This is a two-arm, single blind, superiority, randomised control trial to assess the effectiveness of the intervention arm (RBT and MHFA), relative to the control arm (MHFA alone) on the respective primary and secondary outcomes for business advisors and their SME-owner clients. Using a mixed-methods approach, we will collect quantitative survey data from business advisors and their SME owner clients and qualitative data from interviews with business advisors, SME-owners, instructors, training vendors, and the accounting and bookkeeper member bodies (Supplementary file 1).

### Recruitment

#### Business advisory professionals

The recruitment of business advisors into the online training program, Counting on U, will be conducted over 18 months via membership of their respective professional organisation (i.e., Chartered Accountants of Australia and New Zealand (CAANZ), Certified Practicing Accountants (CPA) Australia, Institute of Public Accountants (IPA), Institute of Certified Bookkeepers (ICB)). Representatives from each organisation will invite their members via email to participate in the training and research program. The project will also be advertised through Deakin University and professional organisations’ newsletters, websites, and social media pages.

Convenience sampling will be used, with all respondents who meet the inclusion criteria offered places in the training program until a total of 984 participants have been recruited. The research team will monitor the participants’ location in urban/regional/rural areas and state, and if a selection bias has occurred, advertising will be targeted to these underrepresented groups. All business advisors will be requested to complete a short online survey at three time-points: baseline, 2 months, and 6 months post-training (equivalent to 1- and 5-months follow-up post-training) (Figs. 1 and 2).

**Fig. 1 Fig1:**
[figure not shown]
Counting on U schedule of enrolment, interventions, and assessments

**Fig. 2 Fig2:**
[figure not shown]
CONSORT diagram showing the enrolment, allocation, quantitative and qualitative data collection time points for the business advisors and their SME-owner clients

#### SME owners

Business advisors will be asked to invite their SME owner clients to take part in the study to help assess the effectiveness of the training from the perspective of someone who is expected to benefit from it. The SME owner clients will complete 3 online surveys at baseline, 6 and 12 months (or 5- and 11 months follow-up post-training). Business advisors will be requested to send a pre-prepared email to 2–5 of their SME owner clients inviting them to participate (Figs. 1 and 2). However, this is not a mandatory requirement for business advisors.

### Inclusion criteria

The business advisor sample will be selected according to the following inclusion criteria: any qualified business advisor from Australia or New Zealand who provides business-related advice to a small-medium enterprise (SME) client. Business advice refers to the information, guidance and/or assistance provided by an external advisor that either directly or indirectly helps to prevent/reduce the financial pressures experienced by SME owner-clients. The SME owner client must be the owner-manager of the business (i.e., non-operational owners or ‘silent partners’ are not included) and the business needs to employ 1–199 employees. The business advisor must be in contact with their client at least three times a year. The exclusion criteria will be any business advisor who has completed Mental Health First Aid training within the last two years.

Because of our recruitment strategy, eligible participants will be randomised to one of two arms prior to receiving a generic invitation to join the study. They will be informed what study arm they are in, after they have agreed to participate. Thus, participants will only be blind to group allocation prior to providing consent to avoid self-selection bias. Participants must read a plain language statement and sign an online consent form hosted by Deakin University prior to starting (Supplementary file 2). Participants can withdraw at any time by contacting the research team at Deakin University.

### Intervention conditions

#### Relationship building and Mental Health First Aid training

Business advisors randomised to the intervention arm will attend Relationship Building Training (RBT) over a 2-hour live zoom session. The module, which will be delivered by qualified instructors, aims to equip business advisors with the skills they need to enhance trustworthiness, reduce information asymmetry and how to harness their communication skills when having a difficult conversation about finances or mental health with their clients. The RBT module’s content was developed by the principal investigators (AN, GT) and is partially drawn from a post-graduate client relationship building unit taught to accountants and financial planners at Deakin University. This module will be followed by a global, certified, blended Mental Health First Aid (MHFA) training program [20]. The training requires 5 hours of online course work followed by 2 × 2.5-hour live zoom sessions delivered by qualified instructors. MHFA aims to enhance mental health literacy, teach business advisors the skills to identify the signs of mental health conditions, and how to have a conversation with SME owner clients who may need professional help. Participants will also attend 2 × 1-hour Booster sessions 1 and 3-months after completing the training. These booster sessions aim to give participants the opportunity to consolidate their learning, to identify factors that help or hinder the transfer of learning into a change in behaviour and to share experiences on how to maximise their learning. The importance of the business advisors using self-care to protect their own well-being will be reinforced in the RBT and Booster sessions.

#### Mental Health First Aid control group

Participants in the control group will complete the MHFA training alone and attend the two MHFA Booster sessions only.

## Measures

Demographic information including age, sex, and residential data will be collected from the registration forms. The training will have direct effects on the business advisors and in turn, have indirect effects on their SME owner-clients. For this reason, the outcomes measured from business advisors are classed as primary, and for the SME owners they are secondary.

### Primary outcomes for business advisors

#### Quality of the relationship

At each of the data collection points, the quality of the relationship between the business advisor and their SME owner clients will be measured using a Quality of the Relationship Questionnaire. The questions will measure the business advisor’s belief about how much attention they are giving their clients, their awareness about their client’s financial and emotional needs, the quality of the advice they provide and the impact they have on their business. Ten items will be used, four are from the Relationship Flourishing Scale [24] that has a Cronbach’s alpha of 0.93, and six are from a validated newly developed tool by the principal investigators (AN, GT) with factor loadings ranging from 0.81 to 0.87. The Relationship Flourishing Scale has demonstrated acceptable concurrent, convergent and content validities [24]. All items are on a 7-point Likert scale (1 strongly disagree, 7 strongly agree) with a higher total score indicating a higher quality relationship.

#### Stigmatising attitude

The business advisors personal stigmatising attitude will be measured at each time point using eight statements that queries the respondent’s opinion of a person described in a modified vignette (personal stigma) [25]. The statements are based on those developed by Griffiths et al., who also reported on their psychometric properties, showing moderately high convergent validity and acceptable Cronbach alphas of 0.78 to 0.82 [26]. The vignette portrays a 35-year-old business owner who is showing signs of depression. An example of a personal stigma item is: “A problem like John’s is a sign of personal weakness”. All 8 items will be scored on 5-point Likert scale (1 strongly agree, 5 strongly disagree), with a higher score indicating stronger stigmatising attitudes.

Previous work has shown that the 8 items are multi-dimensional and by grouping certain items  they can provide two distinct stigma dimensions “weak-not-sick” and “dangerous/unpredictable” [27, 28]. “Weak-not-sick” suggests the problem portrayed in the vignette is a personal weakness under the control of the person rather than as a medical condition. While “dangerous/unpredictable” characterizes the vignette character as unpredictable and dangerous. These two dimensions can inform whether participants better understand mental health is not a sickness but are still fearful of their behaviour. A factor loading analysis will be conducted to assess which items best load onto each dimension and a total mean and standard deviation score will be generated for each.

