#### Financial wellbeing

The financial wellbeing of the SME owners will be measured at each time point using the Perceived Financial Wellbeing Questionnaire [31]. The SME owners must consider how much they agree with 5 statements such as “I am behind with my finances”. Their answers will be scored on a 5-point Likert scale (1 strongly agree, 5 strongly disagree) and a lower total mean score will indicate a more positive outlook. Perceived financial well-being is a strong predictor of overall well-being and the items have a Cronbach’s alpha of 0.86 to 0.94 [31]. The questionnaire has demonstrated discriminate and incremental validity [31].

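### Stigma, a primary outcome, has printed response codes that contradict the stated direction of its score, and the one financial wellbeing item shown has the same conflict

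*Protocol article*

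**What the plan says.** **Stigma.** The Abstract's Methods paragraph lists "stigmatizing attitude, confidence to offer mental health first aid" among the primary outcomes, all measured in business advisors. The Stigmatising attitude section gives codes and direction in one sentence: "All 8 items will be scored on 5-point Likert scale (1 strongly agree, 5 strongly disagree), with a higher score indicating stronger stigmatising attitudes". The example item is "A problem like John’s is a sign of personal weakness". The section goes on to plan two dimensions, with items assigned by a factor analysis and a mean score for each. The Background expects the combined training (relationship building plus mental health first aid) to "decrease any stigmatizing attitudes they may have (e.g., depression is a sign of personal weakness").

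**Financial wellbeing.** This is a secondary outcome, measured in the small-business owners. The section of that name describes five items and prints one, "I am behind with my finances". It gives the scoring as "1 strongly agree, 5 strongly disagree) and a lower total mean score will indicate a more positive outlook".

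Neither section mentions reverse scoring.

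**The concern.** An advisor who strongly agrees that the vignette character's problem "is a sign of personal weakness" gives the most stigmatising answer available and receives the lowest code. The text then reads low scores as weak stigma. An owner who strongly agrees with "I am behind with my finances" also receives the lowest code, and the text reads low scores as the favourable end.

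The Statistics section tests each outcome through the interaction of allocation and time, so the sign of that term carries the conclusion. If the raw codes went into the model and the printed label were attached, a true fall in stigma on such items would be reported as a rise on a primary outcome. The tests are two-sided, so the size and p value of the result would give no warning. The Trial governance section also promises interim data analysis and any unintended effects in an annual report, so a mislabelled score could mislead before the final analysis if those data are shown by arm.

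**Working it through.** **1. Stigma: put the printed codes into the printed item.**

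| Answer to the example item | Meaning of the answer | Code as printed | How the text reads that code | 6 minus code |
|---|---|---|---|---|
| Strongly agree | Most stigmatising | 1 | Weakest stigma | 5 |
| Strongly disagree | Least stigmatising | 5 | Strongest stigma | 1 |

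Only the last column agrees with the stated direction.

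**2. Effect on the treatment contrast.** Let Y be the mean of raw codes over items worded like the example, and Y* = 6 − Y the reversed score. The contrast is the change from baseline in the combined arm minus the change in the control arm.

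- For each arm, Y*(t) − Y*(0) = [6 − Y(t)] − [6 − Y(0)] = −[Y(t) − Y(0)]. The 6 cancels.
- So contrast* = −contrast.
- Var(6 − Y) = Var(Y), so the standard deviation and standard error are unchanged.
- The absolute standardised effect and the two-sided p value are therefore the same, and only the sign differs.

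This assumes a model for mean change on the score's own scale, which is how the Statistics section describes the comparison.

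**3. Financial wellbeing: what the one printed item allows.** Let k of the five items be worded like the printed one, where agreement means trouble, and 5 − k be positively worded. The printed item makes k at least 1. Suppose finances improve by the same amount δ on every item (an assumption). Raw codes rise by δ on the k items and fall by δ on the rest, so the raw mean moves by (k − (5 − k))δ/5 = (2k − 5)δ/5. Scored correctly in the stated direction (lower is better), it should move by −δ.

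| k | Movement of the unreversed mean | Against the correct −δ |
|---|---|---|
| 1 | −0.6δ | right sign, diluted |
| 2 | −0.2δ | right sign, nearly cancelled |
| 3 | +0.2δ | wrong sign, nearly cancelled |
| 4 | +0.6δ | wrong sign, diluted |
| 5 | +1.0δ | fully inverted |

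No admissible k gives the correct result without reversal, but full inversion needs k = 5.

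**4. Comparison with the other scales.** Both Quality of the relationship sections and the Trust section put strong disagreement at 1 and read a higher total as better, which is coherent. The Provision of Mental Health First Aid section says explicitly how answers are converted before summing. A reader therefore has no cue to assume an unstated recode for stigma or financial wellbeing.

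**5. Sample size.** From the Sample size and power analysis section: difference 1.52, SD 7.60, two-sided α 0.05, power 80%. With d = 1.52/7.60 = 0.20, n per arm = 2(1.960 + 0.842)²/0.20² = 2 × 7.85/0.04 ≈ 392.5, rounded up to 393, or 786 in total as stated. For 20% attrition, 393/0.80 = 491.25, rounded up to 492 per arm, or 984 as stated. This calculation is for quality of the relationship and does not use either scale at issue.

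**The case against.** The best reply is that the stigma section gives two statements, the anchors and the direction of the final score, and an analyst who takes the direction as binding will recode and get the right sign. Item-level recoding of a published instrument is often left to a codebook or analysis plan, which is not shown here. The Background states that stigma should fall, so a reversed label has a fair chance of being caught. Stigma is one of several primary outcomes and not the one used for sizing. For financial wellbeing, four of five items are unseen; if they are positively worded, the stated direction is right for the scale and only the printed item needs reversing.

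Much of this stands, and it rules out three stronger readings that a reader might draw:

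- **That the plan prescribes the wrong sign.** It does not. It contains two statements that conflict, and the sign flips only if the raw codes are used and the label is attached unchecked. The survey or code may already be right.
- **That the whole financial wellbeing scale is inverted.** One item of five is evidence about that item only.
- **That the error has a known size in points on an eight-item total.** The section defines no such total and speaks of a mean for each of two dimensions.

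The reply does not remove the point. A fuller document could supply a missing detail, but here nothing is merely missing: the article chose to state anchors, an item and a direction, and they do not fit together.

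**Conclusion.** The point holds for stigma as an internal contradiction in the scoring of a primary outcome. For items worded like the printed one, scoring the raw codes and reading them as labelled reverses the sign of the effect and leaves its absolute size and two-sided p value unchanged. How far this reaches across the eight items depends on their wording. Both dimensions are described by stigmatising content, which suggests similar wording, but only one item is printed.

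For financial wellbeing the firm claim is narrower: the printed item does not run in the stated direction. If all five items are worded like it, the scale is inverted. If some are positively worded, an unreversed mean mixes directions and dilutes the effect, with the wrong sign once three or more items resemble the printed one (under equal shifts on all items).

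Sample size and power do not change. Whether the error exists in the fielded survey or the scoring code, or only in the article, cannot be told from the document.

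**What to change.** First check the anchors that respondents actually see in the survey.

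- **Stigma:** if the survey runs from disagreement to agreement, correct the printed anchors. If the anchors are as printed, either recode each item where agreement is stigmatising as 6 minus the response, or keep the codes and state that a lower score means more stigma.
- **Financial wellbeing:** list which of the five items are reverse-scored so that all run the same way, and state that direction. The Financial distress section reads higher as better, so the text should make plain whether the two scales run in opposite directions.
- **Both:** state which sign of the group-by-time term favours the combined training.

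Fix the scoring code before any by-arm analysis, including any interim data shown by arm in the annual report. The cost is about two sentences and a line of recoding, with no change to the surveys, data collection or sample size.
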